## Methods

### Design

This is a multicenter, prospective, double-blind, phase III clinical trial. Three centers are involved in enrollment (IRCCS Policlinico S. Matteo, Pavia, Italy; Azienda Ospedaliero-Universitaria di Parma, Parma, Italy; and Humanitas Research Center, Milano, Italy), and two centers will be in charge of genetic analyses (Azienda Ospedaliero-Universitaria di Parma) and oxidative stress analyses (IRCCS San Raffaele Pisana, Rome, Italy).

The present study is part of a wider project approved by and funded with a grant by the Italian Health Ministry (“New nanotechnology and biomedical approaches to improve postoperative pain treatment reducing risks related to opioids” - GR-2010-2318370; Principal Investigator [name]).

This clinical study is locally approved by the institutional review boards of promoting and participating centers (Comitato di Bioetica – Fondazione IRCCS Policlinico S. Matteo; Comitato Etico per Parma – Azienda Ospedaliero-Universitaria di Parma; and Comitato Etico indipendente – IRCCS Istituto Clinico Humanitas; reference number PT-SM-13-YR). The trial is registered on ClinicalTrials.gov (NCT02002663; Principal Investigator [name]).

### Patients

Patient eligibility is assessed at the pre-operative anesthesia consultation. All eligible patients must sign a specifically designed informed consent form.

Male and females, American Society of Anesthesiologists I-II-III, from 18 to 85 years old, scheduled to use patient-controlled analgesia (PCA) with morphine for postoperative pain control after major abdominal surgery by laparotomy (gastric surgery, bilious-pancreatic surgery, hepatic resections, bowel resections, nephrectomy, or any laparotomy with intra-peritoneal access) are enrolled.

Regular use of opioid analgesics, history of drugs or alcohol abuse (or both), postoperative hospitalization in intensive care with sedation or mechanical ventilation (or both), neurological disorders, any heart conduction disease, any cognitive or mental disorder hindering a patient from providing informed consent, body mass index of more than 30, diabetes (type I or II), allergy to study drugs, and use of epidural analgesia are exclusion criteria.

### Procedures - clinical study

On the day of surgery, patients come to the operating room and are provided with standard monitoring (electrocardiogram, oxygen saturation, non-invasive blood pressure, and invasive pressure monitoring). General anesthesia is given using propofol and midazolam (as deemed appropriate by the anesthesiologist), opioids (fentanyl 0.2 μg/kg or remifentanil 0.1-0.25 mg/kg per min or both), and muscle relaxants (cisatracurium/rocuronium) and maintained with sevoflurane.

A morphine bolus of 0.15 mg/kg is given 30 to 45 min before the end of surgery. An infusion catheter (Baxter Painfusor®; Baxter International, Deerfield, IL, USA) is placed by the surgeon in the fascial plane between peritoneum and fascia trasversalis, and a 10-ml bolus of 0.2 % ropivacaine is administered immediately after muscular plane closure; the catheter is then connected to an electronic pump (CADD®-Solis; Smiths Medical, Dublin, OH, USA) to give a continuous infusion of pain medications.

During the first 24 h, all patients receive ropivacaine 0.2 % + methylprednisolone 1 mg/kg, 10 ml/h (total volume of 240 ml in 24 h) continuous wound infusion; additionally, either acetaminophen 1000 mg or ketorolac 30 mg every 8 h is prescribed.

### After 24 h, patients are randomly assigned between two groups of treatment:

Treatment group: 10 ml/h continuous infusion of ropivacaine 0.2 % + methylprednisolone 1 mg/kgPlacebo group: 10 ml/h continuous infusion of saline 0.9 %.

Regardless of treatment group, rescue analgesia in the first 48 h is provided by PCA pump with morphine (0.5 mg/ml, bolus 1 mg, lock-out 5 min, 20 mg limit every 4 h).

Random group allocation of patients is made through a computer-generated sequence. To maintain blinding, a research fellow who is not taking part in patient evaluation is in charge of preparing and programming all of the pumps used during the study: an opaque, sealed, sequentially numbered envelope is assigned to each patient and is opened by the same research fellow after the first 24 h of treatment.

Patients and their anesthesiologists are blind to treatment assignment. A clinical resident, who is not involved with randomization, is in charge of all clinical evaluations as part of the daily clinical practice.

The envelope is maintained apart from the patient’s case report form and is to be opened in every potentially harmful situation for the patient but only when care providers need to be aware of the patient’s treatment. All ropivacaine and methylprednisolone vials used during the study are registered with their code in order to be tracked and recognized in the future for any issue potentially hindering the validity of data.

At 48 h, morphine PCA is removed, and all patients are treated with Patient-Controlled Intrawound Analgesia (PCA through the wound catheter) with either ropivacaine 0.2 % alone or saline according to the group of randomization up to a maximum of 7 days after surgery. The catheter is removed at the seventh postoperative day or after 36 h of non-use (no self-administered bolus). After PCA removal, rescue additional analgesia is provided by tramadol (100 mg or 50 mg according to patient’s weight of not more than or of more than 50 kg).

All patients are evaluated at the end of surgery, at 3, 6, 12, 24, 36, and 48 h, and daily to the seventh postoperative day or until catheter removal by the Acute Pain Service and twice a day by the surgeons as part of their current clinical practice. Pain values, analgesic consumption, any drug-related side effect, and any catheter-related complication (such as occlusion or dislodgment) are recorded. Patients are also evaluated by surgeons after discharge, as in the current practice: any infection or healing retardation is monitored, together with any pain or sensorial abnormality to be signaled to the pain practitioners. Regardless, the Acute Pain Service investigates pain persistence at 1 and 3 months through a phone call, and patients with PPSP (patients experiencing pain at 1 or 3 months after surgery) are eventually referred to our pain clinic for evaluation and treatment.

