## Trial status

The trial is currently running, all three centers are currently involved in enrollment, and we have enrolled 46 patients so far.

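### The rescue tramadol rule, read in the order printed, gives the larger dose to lighter patients; it is probably a transposition and should be checked and corrected

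*Protocol article*

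**What the plan says.** The rule is in the protocol article's Methods, at the end of the treatment description under *After 24 h, patients are randomly assigned between two groups of treatment*. Rescue analgesia after PCA removal is "tramadol (100 mg or 50 mg according to patient’s weight of not more than or of more than 50 kg"). The sentence gives two doses in one order and two weight bands in another list, with no word tying the first to the first. The tramadol dose appears nowhere else in the article.

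The other doses given to patients are:

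- **Per kilogram** (*Procedures - clinical study*): the anaesthetic opioids; morphine before the end of surgery, "A morphine bolus of 0.15 mg/kg is given 30 to 45 min before the end of surgery"; and the steroid in the wound infusion, "methylprednisolone 1 mg/kg, 10 ml/h (total volume of 240 ml in 24 h) continuous wound infusion".
- **Flat** (same section): "either acetaminophen 1000 mg or ketorolac 30 mg every 8 h is prescribed".
- **Flat** (treatment-groups section): rescue in the first 48 h by "PCA pump with morphine (0.5 mg/ml, bolus 1 mg, lock-out 5 min, 20 mg limit every 4 h").

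**The concern.** The natural way to read two short parallel lists is first with first and second with second. That gives 100 mg to patients of 50 kg or less and 50 mg to those above 50 kg. A weight rule for an opioid would be expected to run the other way, and the article gives no reason for a dose that falls with weight.

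What is at stake is patient care. Followed in the printed order, the rule gives the lightest patients twice the rescue dose of everyone else, after laparotomy, in a trial that admits patients up to 85 years old and ASA class III. The statistical comparison is not at stake: the rule is common to both arms, and the section lists consumption among the data collected ("Pain values, analgesic consumption, any drug-related side effect, and any catheter-related complication (such as occlusion or dislodgment) are recorded").

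**Working it through.** **Inputs.** The doses are 100 mg and 50 mg and the cut-point is 50 kg, all from the tramadol sentence. The article reports no body weights, so every individual weight and weight range below is an assumption for illustration. No dosing interval is used, so all figures are per single dose.

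**Step 1: bounds that need no assumed weights.** Dose per kg = dose / weight.

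- Printed order, 50 kg or less: at least 100/50 = 2.0 mg/kg. Above 50 kg: under 50/50 = 1.0 mg/kg.
- Reversed pairing, 50 kg or less: at least 50/50 = 1.0 mg/kg. Above 50 kg: under 100/50 = 2.0 mg/kg.

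**Step 2: illustrative patients (mg/kg per dose).**

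| Weight (assumed) | Printed order | Reversed pairing |
|---|---|---|
| 40 kg | 100/40 = 2.50 | 50/40 = 1.25 |
| 50 kg | 100/50 = 2.00 | 50/50 = 1.00 |
| 51 kg | 50/51 = 0.98 | 100/51 = 1.96 |
| 70 kg | 50/70 = 0.71 | 100/70 = 1.43 |
| 80 kg | 50/80 = 0.63 | 100/80 = 1.25 |

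In the printed order a 40 kg patient receives 2.50/0.625 = 4 times the mg/kg dose of an 80 kg patient. With the pairing reversed, both receive 1.25 mg/kg.

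**Step 3: spread across a population.** This is the highest mg/kg divided by the lowest, for three assumed weight ranges. The reversed column uses whole-kilogram weights; its extremes are at 51 kg and 50 kg.

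| Range | Printed order | Reversed pairing | Flat dose |
|---|---|---|---|
| 45–80 kg | (100/45)/(50/80) = 3.56 | (100/51)/(50/50) = 1.96 | 80/45 = 1.78 |
| 40–90 kg | (100/40)/(50/90) = 4.5 | 1.96 | 90/40 = 2.25 |
| 40–100 kg | (100/40)/(50/100) = 5.0 | 1.96 | 100/40 = 2.5 |

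The printed order has exactly twice the spread of a flat dose in every row. This follows from algebra: (100/w_min)/(50/w_max) = 2 × w_max/w_min for any range spanning 50 kg. The three ranges are therefore not three pieces of evidence. They show one thing, that the printed rule makes exposure per kg less even than having no weight rule.

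**Step 4: comparison with the other doses.** The per-kilogram doses rise with weight, and the remaining postoperative analgesics do not vary with it. In the printed order, tramadol would be the only drug whose dose falls as weight rises. The result is the same whether the PCA being removed is the morphine pump at 48 h or the later patient-controlled wound infusion.

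**The case against.** The strongest reply is that this is a slip of wording and not a design decision. Without *respectively* the order need not bind, and the sensible pairing, 50 mg for lighter and 100 mg for heavier patients, is compatible with the sentence. The article condenses a fuller protocol ("This clinical study is locally approved by the institutional review boards of promoting and participating centers"), and staff may work from a correct version of it. Nothing shown establishes that any patient was misdosed, or which pairing was intended.

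Much of this stands. The intended pairing is an inference, harm is only a possibility, and the point has no bearing on the trial's conclusions. It does not remove the need to correct the sentence. Condensing explains what an article leaves out, but this rule is stated in full, and an opioid dosing rule that is either inverted or ambiguous needs rewording in both cases.

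A second objection concerns the spread figures. The factor of two holds by construction, and in the narrowest assumed range the reversed rule (1.96) also spreads mg/kg slightly more than a flat dose (1.78). That is right. The spread is supporting arithmetic only and does not show that the reversed rule is optimal. The case for a transposition rests mainly on direction: the dose falls with weight, no reason is given, and no other dose in the article behaves that way.

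**Conclusion.** The concern holds as a minor correction. Read in its listed order, the sentence gives 100 mg at or below 50 kg and 50 mg above, that is at least 2.0 mg/kg against under 1.0 mg/kg per dose. These bounds need no assumption about patient weights; the spread ratios do.

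Confidence is high that the sentence as printed is wrong or unclear. It is lower for the exact wording intended, which the article alone cannot settle. No effect on the between-arm comparison or the primary endpoint is claimed, and centre practice is unknown.

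**What to change.** Check the sentence against the full protocol and restate it with each weight band next to its dose. The intended rule is apparently: tramadol 50 mg if weight is 50 kg or less, 100 mg if weight is more than 50 kg.

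Only if the full protocol has the same wording as the article, notify the three enrolling centres and confirm which rule was applied to patients already treated. At the time of writing the *Trial status* section reports "we have enrolled 46 patients so far".

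The cost is one check and one corrected sentence, plus the centre notice and patient query if that condition is met. Design, sample size and analysis do not change.

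### The tramadol rescue rule as printed gives the larger dose to lighter patients and the smaller dose to heavier patients, probably through a transposition

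*Protocol article*

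**What the plan says.** All references are to the Methods of the protocol article.

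- **When tramadol applies.** The section on random assignment after 24 h says "At 48 h, morphine PCA is removed". From then on patients have the patient-controlled wound catheter (ropivacaine or saline by arm), and rescue is by "tramadol (100 mg or 50 mg according to patient’s weight of not more than or of more than 50 kg". Tramadol is the only opioid rescue stated for this period, and the article mentions it nowhere else.
- **How other analgesics are dosed.** Under Procedures - clinical study, "A morphine bolus of 0.15 mg/kg is given 30 to 45 min before the end of surgery", and "either acetaminophen 1000 mg or ketorolac 30 mg every 8 h is prescribed". Methylprednisolone is given at 1 mg/kg and the intraoperative opioids per kilogram. The morphine PCA setting is the same for everyone: "bolus 1 mg, lock-out 5 min, 20 mg limit every 4 h".
- **Who can be enrolled.** Under Patients, the age range is "from 18 to 85 years old", and "body mass index of more than 30" is an exclusion. No lower limit on weight or body mass index is stated.

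**The concern.** A weight threshold in an analgesic dose is normally there to give lighter patients less. Read in order, this one gives them double. The sentence states an operative dosing rule, so it is an error of content and not a detail left to a fuller document.

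What is at stake is dosing of individual patients: a larger single opioid dose in the lightest patients, and a smaller rescue dose in everyone over 50 kg once morphine PCA has been withdrawn. The treatment comparison is not at stake in the same way, because the rule does not depend on the arm.

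**Working it through.** **1. Reading the rule.** The sentence gives two doses (100 mg, then 50 mg) and two bands (up to 50 kg, then above 50 kg). The only pairing it offers is first with first and second with second:

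- Printed rule: 100 mg if weight ≤ 50 kg; 50 mg if weight > 50 kg.
- Swapped rule: 50 mg if weight ≤ 50 kg; 100 mg if weight > 50 kg.

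**2. Comparison with the other stated doses.** Morphine at closure, methylprednisolone and the intraoperative opioids rise in proportion to weight. The PCA bolus (1 mg), acetaminophen (1000 mg) and ketorolac (30 mg) are flat. None falls with weight.

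**3. Dose per kilogram.** mg/kg = dose ÷ weight. The weights are illustrative assumptions; the article gives no weight distribution.

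| Weight (kg) | Printed (mg/kg) | Swapped (mg/kg) |
|---|---|---|
| 45 | 100/45 = 2.22 | 50/45 = 1.11 |
| 50 | 100/50 = 2.00 | 50/50 = 1.00 |
| 51 | 50/51 = 0.98 | 100/51 = 1.96 |
| 60 | 50/60 = 0.83 | 100/60 = 1.67 |
| 70 | 50/70 = 0.71 | 100/70 = 1.43 |

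Ratio of a 45 kg to a 70 kg patient: printed 2.222/0.714 = 3.11; swapped 1.111/1.429 = 0.78.

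**4. Bound on the excess in light patients.** Any fixed-dose threshold rule gives uneven mg/kg, so the highest exposures under the two rules should also be compared. At whole-kilogram weights the swapped rule peaks at 100/51 = 1.961 mg/kg. The peak under the printed rule depends on the lightest patient treated:

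- 50 kg: 2.000/1.961 = 1.02, an excess of 2%.
- 45 kg (assumed): 2.222/1.961 = 1.13, an excess of 13%.
- 40 kg (assumed): 2.500/1.961 = 1.275, an excess of about 27%.

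**5. Whether the light band can be reached.** Body mass index at 50 kg, for assumed heights:

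- 1.50 m: 50/1.50² = 22.2
- 1.55 m: 50/1.55² = 20.8
- 1.60 m: 50/1.60² = 19.5

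All are eligible under the stated criteria. The share of such patients is not given and is not estimated here.

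**The case against.** The strongest reply is that this is a slip in a condensed article and not a flaw in the trial. The sentence does not say that doses and bands correspond respectively. The article has another slip of this kind: its Statistics section asks for 120 patients in each group, while the Abstract and the Discussion give 120 in total. The full protocol and site orders may well carry the ordinary rule. The Acute Pain Service sees patients at least daily until catheter removal or the seventh postoperative day, and "Pain values, analgesic consumption, any drug-related side effect, and any catheter-related complication (such as occlusion or dislodgment) are recorded", so clinicians are unlikely to apply an odd dose unnoticed. Nothing is claimed about bias, power, endpoint variability or toxicity. The 3.1-fold ratio compares two assumed weights under a rule that was probably never intended, and the peak excess is only 2% at 50 kg itself.

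Much of this stands. A transposition is the likeliest explanation, the article cannot show what the sites did, and the peak comparison is the fairer measure of excess exposure in light patients. Total rescue also depends on how many doses are given.

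It does not rescue the sentence. If order does not assign the doses, the sentence assigns none and still needs correcting. If order does assign them, the rule runs backwards. A drug dose misstated in the Methods warrants correction even when the cause is clerical.

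**Conclusion.** The concern holds. As printed, the tramadol dose falls as weight rises: 100 mg up to 50 kg and 50 mg above, with the mg/kg dose roughly halving between 50 and 51 kg. Relative to the swapped rule, patients of 50 kg or less receive twice the dose per administration and heavier patients half.

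Confidence in the reading is high. That the swapped rule was intended is an inference from the direction of every other dose in the article. Whether any patient was dosed by the printed rule is unknown, because neither the full protocol nor the site orders are shown. The point should be fixed as a matter of patient dosing; it is no threat to the validity of the comparison between arms.

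**What to change.** Check the sentence against the full protocol. Then replace it with an explicit pairing: tramadol 50 mg for patients of 50 kg or less, and 100 mg for patients of more than 50 kg. If the printed pairing is intended, state the reason. The cost is one check and one corrected sentence.

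Only if the full protocol or the site orders carry the printed pairing, notify the three enrolling centers and check tramadol orders in patients already enrolled (46 at publication, per Trial status). Analgesic consumption is already recorded, so this needs no new data collection.

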**Methods/Design:**

After approval by their institutional review board, three hospitals will enroll 120 patients undergoing major abdominal surgery in a randomized, double-blind, phase III study. After a 24-h CWI of ropivacaine 0.2 % + methylprednisolone 1 mg/kg, patients will be randomly assigned to receive either ropivacaine + steroid or placebo for the next 24 h. Then, patient-controlled CWI with only ropivacaine 0.2 % or placebo (according to the group of randomization) is planned after 48 h up to 7 days (bolus 10 ml, lock-out 1 h, maximum dose of 40 ml in 4 h). Morphine equivalent consumption up to 7 days will be analyzed, together with any catheter- or drug-related side effect. Persistent post-surgical pain (PPSP) incidence will also be investigated. Our primary endpoint is analgesic consumption in the first 7 days after surgery; we will evaluate, as secondary endpoints, any catheter- or drug-related side effect, genotype/phenotype correlations between some polymorphisms and postoperative outcome in terms of morphine consumption, development of the inflammatory response, and incidence of PPSP. Finally, we will collect, in a subgroup of patients, wound exudate samples by micro-dialysis, blood samples, and urine samples up to 72 h to investigate local and systemic inflammation and oxidative stress.

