**Discussion:**

This is a phase III trial to evaluate the safety and efficacy of wound infusion with steroid and local anesthetic. The study is aimed also to evaluate how long this infusion has to be maintained in order to maximize effectiveness. Our data are intended to quantify the amount of ropivacaine and methylprednisolone needed by patients undergoing major abdominal surgery, to be stored in a new nanotechnology device for sustained pain treatment after surgery. We also aim to clarify the roles of inflammatory response, oxidative stress, and genetic background on postoperative and persistent pain after major abdominal surgery.

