### Study outcomes

The primary outcome of the study is to investigate whether a wound infusion of local anesthetic and steroid has a higher analgesic efficacy compared with placebo during 7 days following surgery, assessed as analgesic consumption: the primary endpoint will be the reduction of morphine equivalents required in the first 7 days after surgery.

Secondary outcomes will include the differences in analgesia and side effects within 7 days after surgery. We will investigate any difference in pain at rest and movement (i.e., coughing and deep inspiration) by Numeric Rating Scale (11-point scale from 0 = no pain to 10 = worst imaginable pain), additional analgesic consumption, side effects (postoperative nausea and vomiting, sedation, and any signs of local anesthetic or steroid systemic toxicity), and incidence of persistent post-surgical pain. Differences in terms of wound healing or wound infections will be also assessed up to 3 months to assess any local side effect of steroid infusion. The degree of inflammatory response/oxidative stress between groups will be assessed to analyze the effect of CWI with either treatment or placebo. We plan to analyze the combined effect of some polymorphisms (by using a gene-candidate approach) of genes related to the development of PPSP, pain sensitivity, opioid response, and inflammatory reaction.

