## Discussion

Historically, care providers have considered pain a perioperative issue able to influence immediate morbidity, but in the last decade greater attention has been placed on the long-term effects of unrelieved postoperative pain, especially PPSP [4, 5]. Postoperative pain is a composed phenomenon, in which different variables have to be taken into account [28]. Therefore, new multidisciplinary studies should address pain in a different perspective, heading toward a pathophysiological approach to the different components of pain perception and not merely to analgesia expressed as a numeric value in the first days after surgery. Unfortunately, not all of these components are known, and therapeutic approaches still need to be improved.

When clinicians deal with acute postoperative pain, the surgical wound is a pivotal target for analgesia; nociceptors located within the surgical incision are the origin of pain stimuli coming from the periphery, and their prolonged activation is one of the causes of central sensitization. Inflammation also is a main determinant of pain; a lot of mediators are increasingly expressed after tissue injury leading to primary hyperalgesia [12], and IL-1 has been linked to pain persistence [14]; thus, a therapeutic approach specifically aiming to reduce the inflammatory response is rational. CWI with non-steroidal anti-inflammatory drugs seems to provide only partial advantages [11] (because they act only on COX-associated mediators, like prostaglandin E), whereas steroids have a wide anti-inflammatory effect and arguably a great efficacy against pain perception and chronicization [8, 16]. In our study, we decided to test the efficacy of CWI with both local anesthetic and steroids in patients undergoing major abdominal surgery, configuring the first phase III clinical trial on continuous deep wound infusion of methylprednisolone.

Peripheral administration should minimize systemic adverse effects by reducing bioavailability and plasma concentration; otherwise, any data about pharmacokinetics and potential side effects of continuous infusion of steroids are available: we therefore decided to exclude patients with any disease potentially precipitating after steroid systemic absorption, primarily diabetes (type 1 or 2).

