In regard to local side effects, the main concerns are about wound healing and infections potentially associated with immune-modulatory action of steroids. Most of the existing data deal with high doses of systemic steroids [29, 30]. Up to now, few studies have addressed these issues in patients receiving peripheral steroids: these studies are in the orthopedic setting and investigate only clinical effects of a single-shot administration and provide no evidence of increased infections or difficult healing [29, 30]. We therefore plan to clarify the risk/benefit ratio of continuous administration of methylprednisolone, strictly monitoring wound healing and any potentially harmful effect of CWI.

We decided to treat all the patients with 24-h CWI of ropivacaine and methylprednisolone. This will enlarge the sample size for the phase III trial (120 patients) and will allow us to investigate the differences in locally released cytokines according to suspension of local anti-inflammatory treatment after the first 24 h. This, in our opinion, does not configure a methodological bias, as our primary endpoint is analgesic consumption at 7 days, and we will take care to evaluate any statistically significant difference in morphine consumption at 24 h to eliminate any confounding factor this kind of study design may potentially imply.

Furthermore, an ethical issue arises: because CWI with local anesthetics is already documented as a valuable analgesic strategy [8], switching to a saline infusion after 24 h in the control group may be questioned. Otherwise, placebo control is still a key feature for high-quality clinical trials in the perspective of determining the actual effectiveness of treatments. Furthermore, because we are investigating local inflammation, comparing analgesic efficacy with cytokine analysis will help clarify whether the pain-killing effect of CWI is associated either with methylprednisolone’s action or with a “washout” phenomenon (i.e., on the steroid’s effect on cytokine release rather than on cytokine dilution by fluid infusion).

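### In-hospital safety recording is worded to admit only drug- or catheter-related events, so complications outside the named outcomes can go uncounted and the safety comparison loses events and power

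*Protocol article*

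**What the plan says.** Two places in the protocol article limit safety capture by cause.

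- In the follow-up paragraph under the section on the two treatment groups, the in-hospital assessments run from the end of surgery to day 7 or catheter removal. What is captured there is: "Pain values, analgesic consumption, any drug-related side effect, and any catheter-related complication (such as occlusion or dislodgment) are recorded".
- The Abstract, Methods/Design, uses the same qualifier for the endpoint: "we will evaluate, as secondary endpoints, any catheter- or drug-related side effect".

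Other places are wider.

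- Study outcomes lists "side effects (postoperative nausea and vomiting, sedation, and any signs of local anesthetic or steroid systemic toxicity". Nausea and vomiting and sedation carry no causal condition. The toxicity item does.
- Study outcomes also states: "Differences in terms of wound healing or wound infections will be also assessed up to 3 months". No attribution is required.
- The follow-up paragraph says that surgeons monitor any infection or delayed healing, whatever the cause, but only for the period after discharge.
- The Discussion undertakes to watch wound healing and any possible harm of the infusion.

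Safety is a declared aim: "This is a phase III trial to evaluate the safety and efficacy of wound infusion with steroid and local anesthetic".

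**The concern.** When a drug is given by a new route, its harm is most likely to show as an excess of ordinary events in one arm. The Discussion describes the trial as "configuring the first phase III clinical trial on continuous deep wound infusion of methylprednisolone". It also says that the few studies of peripheral steroids are orthopaedic and single-shot. Its sentence on systemic side effects of continuous steroid infusion is garbled, but its use as the reason for excluding patients with diabetes makes sense only if such data are lacking. The route therefore has almost no reference profile against which to judge one event.

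The design gives the assessor little else to go on. Before randomisation all patients receive ropivacaine and methylprednisolone for 24 h. They also have morphine by PCA, and acetaminophen or ketorolac, after a laparotomy. Patients and anaesthesiologists are blind, and the evaluating resident has no part in randomisation. If relatedness decides whether an event is written down, events that look surgical are lost before the arms can be compared.

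**Working it through.** **Step 1. Which in-hospital events does the wording reach?**

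| In-hospital event | On the in-hospital recording list? | Named in Study outcomes without attribution? |
|---|---|---|
| Nausea and vomiting, sedation | If drug-related | Yes |
| Wound infection, impaired healing | Not listed | Yes, up to 3 months |
| Catheter occlusion, dislodgment | Yes | Not applicable |
| Local anaesthetic or steroid systemic toxicity | If drug-related | No, the item is defined by cause |
| Non-wound infection, sepsis, reoperation, other complication called surgical | No | No |

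The last row is the gap. The toxicity row is captured only if someone attributes the sign to a drug. The wound row is protected as an outcome, although the in-hospital recording list should mention it so that the two agree.

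**Step 2. What does a filter on cause do to the comparison?** The document gives no adverse-event rate, attribution rate or safety power, so there is no stated figure to reproduce. Let the true rates be p1 (placebo) and p2 (treatment), and let a blinded assessor record the same share s in both arms.

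- Recorded rates: s·p1 and s·p2.
- Risk ratio: (s·p2)/(s·p1) = p2/p1, unchanged.
- Risk difference: s·(p2 − p1), smaller by the factor s.

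**Step 3. Illustration for events in the gap.** The rates of 10% and 25% and the values of s are assumptions. Arm sizes are 50, the evaluable number in Statistics, and 60, half of the 120 in the Abstract and Discussion. (Statistics also gives 120 for each group, which does not agree with those places.) With a two-sided α of 5% and n per arm:

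power = Φ{(d − 1.96·se0)/se1}, where d = s(p2 − p1), se0 = √[2·p̄(1 − p̄)/n], se1 = √[(q1(1 − q1) + q2(1 − q2))/n], q1 = s·p1, q2 = s·p2 and p̄ = (q1 + q2)/2.

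For n = 60 and s = 1: d = 0.15, se0 = 0.0694, se1 = 0.0680, so power = Φ{(0.15 − 0.1360)/0.0680} = 58.2%.

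| Share recorded (s) | Events per arm, n = 60 | Risk ratio | Risk difference (points) | Power, n = 50 | Power, n = 60 |
|---|---|---|---|---|---|
| 1.00 | 6 v 15 | 2.5 | 15.0 | 50.6% | 58.2% |
| 0.75 | 4.5 v 11.25 | 2.5 | 11.25 | 38.3% | 44.5% |
| 0.50 | 3 v 7.5 | 2.5 | 7.5 | 26.2% | 30.5% |
| 0.25 | 1.5 v 3.75 | 2.5 | 3.75 | 14.7% | 16.9% |

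Even with complete recording, the trial would be underpowered for a difference of this size, so it has few events to spare.

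**The case against.** The strongest reply is that the harms of most concern are already protected. Study outcomes compares wound healing and wound infection up to 3 months whatever the cause, expressly to detect local effects of the steroid. A reader might infer that steroid harms resembling surgical complications drop out of the comparison altogether. The document does not support that, and this part of the reply stands in full.

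A reader might also set the recording list against the Discussion's "the main concerns are about wound healing and infections potentially associated with immune-modulatory action of steroids" and conclude that infections of every kind were promised. That sentence opens by confining itself to local side effects, so it does not show a promise about non-wound infection.

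A third tempting inference is that the filter biases the comparison toward no difference. On the ratio scale it does not, if the same share is recorded in each arm, and blinding makes unequal labelling less likely.

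Finally, no case-by-case causality step is described. The qualifier may be shorthand for a checklist of known drug effects, since nausea and sedation are listed without a causal condition. An article may also leave adverse-event procedures to the full protocol. Both points have force, and the absence of such procedures is not the complaint here. The article does, however, state a restrictive rule twice. Nowhere does it provide for recording in hospital regardless of cause, and it drops the condition for infection and healing only after discharge.

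**Conclusion.** The point holds in a limited form. Read as written, the Abstract and the follow-up paragraph let in-hospital complications go unrecorded when they are neither named outcomes nor attributed to a drug or the catheter. In a blinded trial with a safety aim and a little-studied route, that is a badly fixed rule and should be changed. Wound infection, healing, nausea and vomiting, and sedation are outside the criticism.

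The cost is lost events, a smaller risk difference and lower power, not a distorted risk ratio. Under the assumed rates, recording half the gap events takes power from 50.6% to 26.2% at 50 per arm, and from 58.2% to 30.5% at 60. These figures only show how the loss scales. The conclusion itself rests on two things: that the qualifier is applied literally, and that both arms are filtered alike. If the shares differed between arms, the risk ratio would also shift, but nothing in the document points to that.

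**What to change.** Reword the Abstract endpoint and the follow-up paragraph so that they agree with Study outcomes and with the Discussion's undertaking to watch for any harm:

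- Record all in-hospital adverse events and postoperative complications, including every infection, reoperation and wound event, irrespective of presumed cause.
- Hold causality in a separate field.
- Date onset as before or after the 24 h randomisation, because both arms receive the same infusion until then.
- In Study outcomes, compare the arms on all post-randomisation events. Keep the drug-related subset as a secondary listing.

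The cost is a change to the case report form and more unrelated events to log. Patients are already seen by the pain service at set times and then daily, and by surgeons twice a day, so no visits are added. The article reports 46 patients enrolled, and these may need retrospective capture from charts. On a total of 120, the change would apply prospectively to 120 − 46 = 74 patients (62%).
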